##### HLS-EU-Q16

The European Health Literacy Survey questionnaire describes the ability of citizens to make decisions that are beneficial to their health. The higher the health literacy of the individual, the greater the freedom to make decisions in health matters and the greater the ability to locate, understand, and implement health information. The 16 questions can be answered using a pre-determined 4-point response scale (very easy, fairly easy, fairly difficult, very difficult).

Health economics.

The primary methods for evaluating health economics will include cost-effectiveness analysis (CEA) and cost-utility analysis (CUA). This includes determining the expenses associated with all resources (e.g., personnel resources, including physical therapists and physicians, consumables, overhead) consumed as a patient progresses through a care pathway. This comprises waiting times, length of stay, and transportation. The incremental cost-effectiveness ratio (ICER) will be calculated using the effectiveness of app-based therapy and TAU derived from the primary and secondary endpoints. These results will help rank the digital health app in terms of the cost and effectiveness of vertigo treatment. To calculate the costs of all resources, we will employ time-driven activity-based costing (TDABC), a method that combines process mapping and resource-level costing and has been employed globally to assess healthcare costs.

### Follow-up measures

Follow-up measures will be performed after 2 weeks (T1), 6 weeks (T2), and 12 weeks (T3). Questionnaires will be provided digitally. Patients will input their data into the relevant part of the scales or questionnaires. Blinded investigators will input their data into the CRF. Data quality and compliance will be checked by the monitors. To limit loss to follow-up, we will validate with participants’ contact information at each time point. At T1 and T2, the investigators will check with the participants telemedically. Table 4 and 5 provides information on the frequency and timing of clinical measurements.

**Table 4 Tab4:**
[figure not shown]
Frequency and timing of measurements

### Participant timeline

The schedule of enrolment, interventions, and assessments based on SPIRIT [17] is depicted in Fig. 1. The subsequent scheme shows the overall design and clinical procedures of the study. Major steps are screening, enrollment, allocation, follow-up, and ITT analysis. After screening, the decision on inclusion and/or exclusion is made. The next step is the random assignment and thus the allocation to the experimental group or control group. Within the follow-up, data acquisitions are performed. After 12 weeks the study is completed for each individual patient (Fig. 2).

**Table 5 Tab5:**

Proposed sample size

**Fig. 2 Fig2:**
[figure not shown]
Participant timeline

### Sample size

The proposed sample size is 200, with 100 per group. The primary endpoint (VSS-sf-VER (German version of VSS-G) has a range of 32. Because no empirical data are available, 15% (IQWiG 2022) [59] of the range was chosen as a relevant effect, i.e., 5; the imputation methods are conservative, and the real effect has to have 6. The standard deviation of the change from baseline to week 12 is expected to be less than 12. To account for the reducing effect of replacing missing values or dropouts, a drop outs/imputations-addition is included, resulting in the final case number calculation.

### Data collection and management

#### Plans for assessment and collection of outcomes

Data will be gathered utilizing a digitized CRF. Outcome measurements will be obtained at the time of inclusion and at follow-up points spanning 2 weeks, 6 weeks, and 12 weeks (Fig. 2).

### Plans to promote participant retention and complete follow-up

To minimize the risk of participants being lost to follow-up, we will periodically verify their contact details and preferred mode of communication at each time point. The study database will be maintained at the Tübingen Study Center (TSC), which will securely store all data collected by the CRF on its own servers. All digitized data, including the Trial Master File and patient identification list, will be consolidated into a single file, encrypted, and archived in the TSC clinical information system. The procedure follows the harmonized Standard Operating Procedures (SOPs) of the German Coordinating Centers for Clinical Studies. Data protection follows the European General Data Protection Regulation.

### Data review, database cleaning and issuing and resolving data queries

Deployment of monitors.

### Verification, validation and securing of electronic clinical data systems

After patients and doctors provide data, it will be viewed by a study monitor. Any discrepancies will be identified and addressed directly with the patient or doctor to avoid incorrect data entry based on misunderstandings or errors.

### Specified retention period

All original data will be stored for the longest possible period of time the TSC permits; at least 15 years according to § 26 AMG.

### Confidentiality

At the conclusion of the study, data will be securely stored in the TSC servers in a de-identified format, identified solely by a unique identification code. Only the investigators will possess access to the key that associates these codes with individuals. The protocol, anonymous data, and statistical code supporting the findings of this study will be available from the corresponding author upon reasonable request.

### Plans for collection, laboratory evaluation and storage of biological specimens for genetic or molecular analysis in this trial/future use

N/A. No biological specimens are collected.

### Statistical methods

For descriptive statistics, usual methods will be used for quantitative variables (i.e., means, medians, standard deviations, quartiles, maximum and minimum). For qualitative variables, absolute and relative frequencies will be determined. Furthermore, 95% confidence intervals (CIs) will be calculated where appropriate. Analysis of covariance (ANCOVA) will be used for the analysis of changes from baseline with baseline as a covariate and treatment group as a factor. No formal pre-tests of normality or homoscedasticity are planned; the range of the score data (changes from baseline) is limited without extreme skewness; the homoscedasticity of the 2 groups of changes is given under the assumption of no treatment effect. The sample sizes of about 100 per group make this simple ANCOVA with 1 factor (group) and 1 covariate (baseline) asymptotically robust even in the case of not normally distributed data. Wilcoxon tests will be used for sensitivity analyses. For confirmatory statistics, the following a priori-ordered tests will be used:

#### Primary confirmatory endpoint

Group comparison of the change in VSS-sf-VER from baseline to Week 12. The primary hypothesis to be tested is the equality of the VSS-sf-VER change against the alternative of the superiority of VH-90-D vs. TAU with a two-sided significance level of α = 5%. ANCOVA with experimental group as factor and baseline as covariate and sensitivity analysis with a Wilcoxon rank test stratified by baseline values will also be carried out.

### Secondary confirmatory endpoints

Group comparison of DHI change T0-T3 (ANCOVA), group comparison of CGI-I at week 12 (Wilcoxon-test), group comparison of CGI-S changes T0-T3 (ANCOVA), group comparison of DT changes T0-T3 (ANCOVA), group comparison of VSS-sf-AA changes T0-T3 (ANCOVA), group comparison of SF-36 changes T0-T3 (ANCOVA).

All tests of secondary endpoints (#2–7 above) will be 2-sided tests with *α* = 5%. For handling multiplicity, including alpha error avoidance, the above-listed endpoints will be tested in the above indicated a priori order as long as significance is reached; if significance is not reached for a certain variable, further listed variables can be tested only in a descriptive manner. This a priori rejecting procedure controls the multiple significance level of 5% in a strong sense for all primary and secondary endpoints.

All post hoc tests including subgroup analyses are planned as descriptive statistics with exploratory interpretation of p values and 95% CIs.

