#### Secondary outcome measures

*DHI (*Dizziness Handicap Inventory)*, CGI-I* (Clinical Global Impression I – improvement scale), *CGI-S (Clinical Global Impression – Severity Scale),* NCCN® DT (National Comprehensive Cancer Network Distress Thermometer), VSS-sf-AA, SF-36 (36-Item Short Form Health Survey).

Like the primary outcome measure, secondary outcomes will also be evaluated by the authors.

Dizziness Handicap Inventory (DHI)/vertigo handicap.

The Dizziness Handicap Inventory (DHI) is a 25-item, self-reported questionnaire that evaluates the impact of dizziness/vertigo on quality of life and can be used to assess the severity and effect of therapeutic treatments. Each item is rated on a 3-point scale. A higher total score reflects a more severe handicap. The DHI comprises items on three subscales: emotional (DHI-E: anxiety or mental stress influenced by dizziness or vertigo), functional (DHI-F: disability affecting daily living caused by dizziness or vertigo), and physical (DHI-P: dizziness or vertigo provoked by specific self-motions) [31–39, 41–45]. The reliability and validity of the German version have been demonstrated [46]. Cronbach alpha values for the DHI-G and the functional, physical, and emotional subscales were 0.90, 0.80, 0.71, and 0.82, respectively. The limits of agreement were 12.4 points for the total scale (maximum 100 points). Intraclass correlation coefficients ranged from 0.90 to 0.95.

CGI-I/change in vertigo.

The Global Index of Improvement (CGI-I) on the Clinical Global Impression (CGI) questionnaire is a tool to record disease improvement in terms of disease severity and response to therapy [41–45, 47, 48]. The patient's present overall clinical condition is compared to the 1-week period just prior to initiation of the intervention (baseline visit). The query is rated on a 7-point scale: 1 = very much improved since the initiation of treatment; 2 = much improved; 3 = minimally improved; 4 = no change from baseline (the initiation of treatment); 5 = minimally worse; 6 = much worse; 7 = very much worse since the initiation of treatment.

CGI-S/vertigo severity.

The Global Index of Severity (CGI-S) is the second tool of the CGI questionnaire, recording disease severity and response to therapy [43]. The CGI-S is based on the following 7-point scale: 1 = normal, not at all ill; 2 = borderline mentally ill; 3 = mildly ill; 4 = moderately ill; 5 = markedly ill; 6 = severely ill; 7 = among the most extremely ill patients.

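### CGI-I, step 3 of the fixed sequence, is the only confirmatory endpoint whose named test has no baseline term; adjusting for T0 CGI-S could add power at little cost

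*Protocol article*

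**What the plan says.** All references are to the protocol article.

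- **Secondary confirmatory endpoints** lists the "group comparison of CGI-I at week 12 (Wilcoxon-test") directly after DHI and directly before the "group comparison of CGI-S changes T0-T3 (ANCOVA"). With the primary endpoint as number 1, the order is VSS-sf-VER, DHI, CGI-I, CGI-S, DT, VSS-sf-AA, SF-36.
- **Statistical methods** defines the model for the other six: "Analysis of covariance (ANCOVA) will be used for the analysis of changes from baseline with baseline as a covariate and treatment group as a factor".
- **Primary confirmatory endpoint** adds, for VSS-sf-VER only, a "sensitivity analysis with a Wilcoxon rank test stratified by baseline values will also be carried out".
- **Secondary confirmatory endpoints** fixes the level, "All tests of secondary endpoints (#2–7 above) will be 2-sided tests with" α = 5%, and the stopping rule: "if significance is not reached for a certain variable, further listed variables can be tested only in a descriptive manner".
- **Secondary outcome measures** defines CGI-I as a seven-point rating in which the patient's "present overall clinical condition is compared to the 1-week period just prior to initiation of the intervention (baseline visit").

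**The concern.** CGI-I has no baseline value of its own, so it cannot enter an ANCOVA of change as the other endpoints do. CGI-S belongs to the same questionnaire and must be recorded at T0, since its T0 to T3 change is the next endpoint. If patients who start out more or less severely ill tend to receive different CGI-I ratings, T0 CGI-S explains part of the spread in CGI-I. A test that ignores it is then less powerful than it could be.

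The position in the sequence gives this some weight. A non-significant CGI-I leaves four endpoints (CGI-S, DT, VSS-sf-AA, SF-36) descriptive only. The authors clearly know baseline-stratified rank tests, since they name one for the primary endpoint.

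**Working it through.** **Step 1: the plan's own figure.** The Sample size section gives 100 per group, a relevant effect of 5 points, a real effect of 6 points, and an SD of change below 12. All of these concern VSS-sf-VER. With SD 12 and two-sided 5%, n per group = 2(z₀.₉₇₅ + z_power)² × SD²/Δ²:

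- Δ = 5, power 80%: 2 × 7.849 × 144/25 = 90.4, so 91. With 10% dropout, 91/0.9 = 101.1, so 102.
- Δ = 6, power 90%: 2 × 10.507 × 144/36 = 84.1, so 85. With 15% dropout, 85/0.85 = 100.
- Power at 100 per group: 83.8% for 5 points, 94.2% for 6 points.

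The stated size is consistent with such inputs. The power target and dropout rate cannot be read in the copy at hand, so it cannot be reproduced uniquely. Nothing is stated for CGI-I: no effect, no distribution, no correlation with T0 CGI-S.

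**Step 2: assumptions for CGI-I.** The standardised effects d = 5/12 = 0.417 and d = 6/12 = 0.5 are borrowed from the primary endpoint. The correlation r between baseline severity and CGI-I on a latent normal scale is varied from 0 to 0.5.

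**Step 3: analytic approximation.** The Wilcoxon efficiency on a normal latent scale is 0.955, and adjustment leaves a share 1 − r² of the variance. Power = Φ( d / √[2(1 − r²)/(0.955 × 100)] − 1.96 ). Example, d = 0.417, r = 0.3: √(2 × 0.91/95.5) = 0.138; 0.4167/0.138 = 3.02; Φ(1.06) = 85.5%.

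| d | no adjustment | r = 0.2 | r = 0.3 | r = 0.4 | r = 0.5 |
|---|---|---|---|---|---|
| 0.417 | 82.1% | 83.6% | 85.5% | 88.1% | 91.4% |
| 0.5 | 93.3% | 94.1% | 95.2% | 96.5% | 97.9% |

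**Step 4: simulation on the seven-point scale**, 100 per arm, 4,000 trials per cell. Assumed control shares for CGI-I grades 1 to 7: 8, 20, 27, 30, 9, 4.5 and 1.5%. Assumed shares for T0 CGI-S grades 1 to 7: 2, 6, 22, 35, 25, 8 and 2%. The Monte Carlo standard error of one entry near 80% is √(0.8 × 0.2/4000) = 0.6 points.

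| d | r | plain Wilcoxon | van Elteren by T0 CGI-S | rank ANCOVA on T0 CGI-S |
|---|---|---|---|---|
| 0.417 | 0 | 78.2% | 76.4% | 78.1% |
| 0.417 | 0.2 | 79.0% | 78.4% | 79.8% |
| 0.417 | 0.3 | 79.9% | 81.6% | 82.9% |
| 0.417 | 0.5 | 78.8% | 87.3% | 88.1% |
| 0.5 | 0 | 91.5% | 90.3% | 91.4% |
| 0.5 | 0.3 | 92.4% | 93.5% | 93.9% |
| 0.5 | 0.5 | 91.9% | 96.3% | 96.4% |

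With no treatment effect, all three tests rejected in about 4.4% to 5.1% of trials.

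**Step 5: proportional-odds model with T0 CGI-S**, d = 0.417, 2,000 trials per cell (standard error √(0.8 × 0.2/2000) = 0.9 points). Plain Wilcoxon versus model: 79.4% vs 79.7% (r = 0), 79.3% vs 81.0% (0.2), 79.9% vs 82.5% (0.3), 81.1% vs 87.1% (0.4), 80.6% vs 89.5% (0.5). Its type I error was not simulated.

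**Step 6: effect on the sequence.** CGI-I is reached only if VSS-sf-VER and DHI succeed. With an assumed residual correlation of 0.6 between endpoints (3,000 trials), the probability of passing steps 1 to 3, plain versus stratified Wilcoxon for CGI-I, is:

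- d = 0.417: 64.3% vs 64.0% (r = 0), 68.2% vs 68.4% (0.2), 68.3% vs 70.0% (0.3), 74.0% vs 80.8% (0.5).
- d = 0.5: 87.9% vs 88.7% (0.3), 89.5% vs 94.1% (0.5).

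**The case against.** The strongest reply is that nothing here is wrong. A two-sample Wilcoxon test suits a seven-point ordinal rating and holds its level. The asymmetry also follows from the plan's own rule: ANCOVA is reserved for changes with a baseline of the same scale. CGI-I has none and is already rated against the baseline week. The plan adjusts no other endpoint for a different scale's baseline. The endpoint list is shorthand, so strata could be named in an analysis plan that is not shown. The gain rests on an unknown correlation, and at low correlation stratification costs power. The borrowed d = 5/12 is pessimistic if the real effect is 6 points with an SD below 12.

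Most of this stands, and it limits the point to a conditional efficiency suggestion. Two parts do not carry through. Being referenced to baseline does not remove dependence on starting severity: change scores are referenced to baseline too, and the plan still adjusts them. The loss at low correlation belongs to the stratified test. Rank ANCOVA and the proportional-odds model lost essentially nothing at r = 0.

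A reader might infer that precision is lost as a matter of fact, or that chance imbalance in severity biases the CGI-I result. The documents support neither. They give no correlation. Eligibility covers 17 diagnostic groups and subgroups by severity are planned, which makes variation in severity plausible but does not show that it predicts CGI-I. Under randomisation, chance imbalance is already covered by the 5% type I error.

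**Conclusion.** The point holds as an optional improvement of low severity. The article names a valid test for CGI-I that leaves out a baseline measure the trial already collects, at a step that decides whether four further endpoints stay confirmatory.

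For d = 5/12, adjustment is worth about 2 to 3 points of power at r = 0.3 and 8 to 9 at r = 0.5. For d = 0.5 it is worth 1 to 2 points at r = 0.3 and about 4 at r = 0.5 (96.4 − 91.9 = 4.5). At r of 0.2 or less it is negligible. Passing the first three steps shows a similarly modest gain unless r is near 0.5. The effect, the correlation, the category shares and the correlation between endpoints are all assumptions. If the unseen analysis plan already adjusts CGI-I for T0 severity, the point is met.

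**What to change.** In Secondary confirmatory endpoints, replace the test named for CGI-I at week 12 by a proportional-odds model, or rank ANCOVA, with treatment group and T0 CGI-S as covariate. Keep the plain Wilcoxon test as sensitivity analysis. Position in the sequence, alpha and two-sidedness stay as they are.

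A van Elteren test stratified by pooled T0 CGI-S categories is a second choice. It needs a pooling rule for sparse grades and may cost 1 to 2 points of power when the correlation is near zero.

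The cost is one line of analysis wording, with no new data or patients. The proportional-odds model adds an assumption, which rank ANCOVA avoids. Timing is the real constraint. Trial status says the article was re-submitted after the close of the study, and Internal validity relies on pre-specification to limit reporting bias. The adjusted test can be confirmatory only if it is fixed before data are analysed by group. If that point has passed, keep the Wilcoxon test as the confirmatory test and report the adjusted analysis as supportive.

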#### Internal validity

The randomization sequence will be established before the study participants are assigned to the different groups. At the time of study inclusion by the study physician, the randomization will still be secret. Thus, the selective selection of study participants into the different treatment groups is sufficiently counteracted.

Due to the lack of blinding of the patients to participation in the app intervention or physiotherapy, performance bias will be present to a certain degree, which has to be accepted due to the impracticable blinding. In the self-reported endpoints (patient-reported outcomes), there is no detection or observer bias. However, the functionality and AE surveys by separate, non-blinded external committee members are subject to detection bias. This is acceptable in that the functionality and AE survey is descriptive and do not include confirmative endpoints. Reporting bias will be minimized through pre-specification of the primary and secondary confirmative endpoints and statistical procedures including statistical handling of dropouts.

Attrition bias will be minimized by evaluating the ITT population using multiple imputation as a pre-specified procedure. In addition, the reasons for missing data and drop-outs will be collected and evaluated.

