## Methods

### Study setting and design

This project is a prospective, randomized, group-controlled, single-blinded confirmatory clinical multi-center trial (German Vertigo Study, GEVE II study). Approved by the Ethics Committee of the German State of Baden-Württemberg Chamber of Physicians and Surgeons (F 2021–157) the study has been registered with the German National Registry of Clinical Studies (DRKS00028026). After oral information by a study physician, patients provide written informed consent to participate. In addition to the overall analysis, a separate analysis is planned for the results of each individual center. The scheme in Fig. 1 shows the overall design and clinical procedures of the study. During the follow-up, data acquisition will be performed. After 12 weeks, the study will be complete for an individual patient. If a patient is symptom-free prior to the completion of the study, he/she may discontinue therapy. These patients are not dropouts. After the last patient is out, a complete ITT (intention to treat) analysis will be performed. At T0, study physicians perform the initial clinical assessment in person and submit the results into the uniform online eCRF (electronic case report form, Magana Trial Manager, MaganaMed, Regensburg, Germany). All subsequent data are collected as ePROs using different sections of the same eCRF system. At the designated time points participants receive email links to the questionnaires, along with reminders.

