To minimize stratification bias, block randomization will be performed. A list of blocks will be created by researchers who are not involved in the performance of the clinical study. Allocation concealment will be achieved by envelope concealment as described by Doig and Simpson [30]. As additional security measures, the person creating the envelope will sign the back of the envelope when sealed. The envelope will be opened no earlier than at the end of the T0 visit to allow patients in the IG to be introduced into the app. Randomization will be performed at the end of the T0 visit by an independent research professional not involved in the trial.

Permanent patient blinding is not feasible. Patients will be blinded during the complete enrollment process until the randomization envelope is opened and patients do or do not receive the app. The researchers collecting the clinical study endpoints will be blinded throughout the study. For ethical and practical reasons, a separate external adverse event (AE) monitoring and app dysfunction committee will be established whose members will be assigned to AE patient care, hazard coping, and app support. In case of a serious adverse event, the German National Authority BfArM is informed indicating expectedness, seriousness, severity, and causality. They will not be blinded and will not collect endpoints. Except for medical emergencies, they will not have contact with patients’ prior endpoints retrieved by the blinded staff. They will contact patients in separate sessions.

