The present RCT was developed to overcome these problems. However, though characterized by a confirmatory design, the experimental nature of the trial may introduce bias. This includes the contact with study physicians. Formally not considered a confounder, it could introduce bias. Exposure to study doctors may contribute to better study adherence in the RCT compared with real-life studies. Furthermore, the absence of blinding for patients regarding the care provided may influence their perceptions. However, this approach is deemed essential because patients experience their specific treatment. Nevertheless, due to the nature of the trial, patient awareness of the specific care model they encounter may enhance external validity.

The planned RCT is based on a series of primary and secondary efficacy variables. Vertigo intensity is measured using the German version of the VSS-sf-VER. The factor structure of the VSS and the validity and reliability of the VSS-sf-VER have been assessed for various languages [38], including German [39, 46]. The DHI uses the original three-subscale structure from various factorial solutions of the DHI [38]. The reliability and validity of the German version has been demonstrated [42]. The CGI has been shown to correlate well with standard, well-known efficacy scales (e.g., Hamilton Rating Scale for Depression, Hamilton Rating Scale for Anxiety, Positive and Negative Syndrome Scale, Leibowitz Social Anxiety Scale, Brief Psychiatric Rating Scale, Scale for the Assessment of Negative Symptoms) across a wide range of indications. Although originally developed for psychiatry, it is now also widely used for somatic diseases, including vestibular disease [46]. The DT has been proven to be feasible, accessible, and informative [49, 53]. Vertigo autonomic responses/anxiety are measured using the German version of the validated VSS-sf-AA. The factor structure of the VSS-sf-AA and its validity and reliability have been assessed for various languages, [38] including German [39]. The SF-36 Health Survey is a widely used classical and validated inventory.

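### The plan declares its self-reported endpoints free of detection bias, although the patients who rate them know their arm

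*Protocol article*

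**What the plan says.** The Study interventions section of the protocol article states: "Permanent patient blinding is not feasible". Patients are blinded only until the envelope is opened at the end of the T0 visit. Internal validity draws one consequence: "Due to the lack of blinding of the patients to participation in the app intervention or physiotherapy, performance bias will be present to a certain" (the sentence goes on to accept this as unavoidable). The next sentence then says: "In the self-reported endpoints (patient-reported outcomes), there is no detection or observer bias". The sentence after that accepts detection bias for the functionality and adverse event surveys, because the committee members who run them are not blinded. The Discussion adds that "the absence of blinding for patients regarding the care provided may influence their perceptions".

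On who records the endpoints, Study setting and design says of everything after T0: "All subsequent data are collected as ePROs using different sections of the same eCRF system". Follow-up measures says: "Blinded investigators will input their data into the CRF". Study interventions says: "The researchers collecting the clinical study endpoints will be blinded throughout the study". Secondary outcome measures describes CGI-I and CGI-S without naming a rater.

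On checking the data, the section on verification of electronic data systems has a study monitor view entries after they are provided: "Any discrepancies will be identified and addressed directly with the patient or doctor". Questionnaire answers are not exempted.

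**The concern.** Detection bias arises when the person who assesses the outcome knows the allocation. In a symptom questionnaire that person is the patient. Blinding the staff who send, receive or file the questionnaire does not change this. The article claims a protection that the design does not have, and does so for the primary endpoint.

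The trial compares a new app with usual physiotherapy, and the primary score is the patient's own account of how often symptoms occurred over the past month. If app users report more favourably than controls for the same symptoms, the ANCOVA contrast includes that difference, and neither the imputation nor the ordered testing removes it. A reader who trusts the sentence would give a superiority result more weight than the design allows.

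Two lesser matters bear on the same issue. If all data after T0 come from patients, the single-blinded label protects no post-baseline confirmatory endpoint. If blinded investigators rate the CGI, the statement that everything after T0 is an ePRO is wrong. And a monitor's query to an unblinded patient about a submitted answer is a possible route for that answer to change.

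**Working it through.** **Part 1: the statements side by side**

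| Question | What the article says | Section |
|---|---|---|
| Do patients know their arm? | Yes, once the envelope is opened | Study interventions |
| Who supplies the questionnaire answers? | The patients, digitally | Follow-up measures; Study setting and design |
| Does a non-blinded assessor imply detection bias? | Yes, for the adverse event and functionality surveys | Internal validity |
| Can the lack of blinding affect what patients perceive? | Yes | Discussion |
| Is there detection bias in self-reports? | No | Internal validity |

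The first four rows imply the opposite of the fifth. The rule that Internal validity applies to non-blinded committee members applies equally to non-blinded patients.

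**Part 2: which confirmatory endpoints are affected**

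The fixed order is VSS-sf-VER, DHI, CGI-I, CGI-S, DT, VSS-sf-AA, SF-36, so there are seven tests.

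- If everything after T0 is an ePRO, all seven are assessed open-label.
- If blinded investigators rate both CGI scales, 7 − 2 = 5 remain open-label, the primary among them.

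The primary endpoint is exposed on either reading. CGI-I and CGI-S are third and fourth, so they also decide whether the last three can be tested confirmatorily.

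A change of rater between T0 and T3 would matter for CGI-S only, because it is analysed as a T0–T3 change. CGI-I is a single score at week 12. For CGI-I the open question is only who gave it.

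**Part 3: illustration of size**

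The article gives no figure for reporting bias, so there is none to reproduce. Inputs:

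- From the article: 100 per group, and SD of change expected to be below 12 (Sample size); two-sided α = 5% (Primary confirmatory endpoint).
- Assumed: no true effect; complete data; a differential reporting bias b of 1, 2 or 3 points in favour of the app; and, as a second case, SD 8.

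Formulas, as an unadjusted normal approximation:

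- SE = SD × √(2/100)
- Two-sided rejection probability = 1 − Φ(1.96 − b/SE) + Φ(−1.96 − b/SE)

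At SD 12, SE = 12 × 0.1414 = 1.697. At SD 8, SE = 8 × 0.1414 = 1.131.

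Worked case, SD 12 and b = 1: b/SE = 0.589. The upper tail is 1 − Φ(1.371) = 8.5%, which is the chance of a false claim for the app (2.5% without bias). Adding the lower tail, Φ(−2.549) = 0.5%, gives 9.1% from unrounded values.

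| Assumed bias b (points) | SD 12 | SD 8 (assumed) |
|---|---|---|
| 0 | 5.0% | 5.0% |
| 1 | 9.1% | 14.3% |
| 2 | 21.8% | 42.4% |
| 3 | 42.4% | 75.5% |

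For scale, the smallest significant observed difference at SD 12 is 1.972 × 1.697 = 3.35 points (1.972 being the t quantile), so one point of bias is 1/3.35 = 30% of it. SD 12 is the article's upper bound. A smaller SD, or a smaller residual SD after baseline adjustment, makes the inflation larger for the same bias.

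**The case against.** The strongest reply is that the article is open about the missing patient blinding. It says so in Study interventions, concedes performance bias in the sentence before the disputed one, and returns to the point in the Discussion. In context, detection or observer bias may have been meant as bias from an outside observer, since the contrast drawn is with external committee members. This stands in part: a reader might infer that the article hides the problem or rules out any effect of expectation, and the text does not support that. But the sentence as written covers the self-reported endpoints without qualification, and the concession names performance bias only.

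On the CGI, no section names two raters, participants complete outcome questionnaires at T0, and the timing tables and figures are not visible here. A reader might infer that physician ratings at T0 are compared with patient ratings at T3, or that two confirmatory tests are invalid. The documents do not support either reading. What stands is a conflict between general statements about the data source, with at most the CGI-S change at risk.

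On monitoring, the stated purpose of queries is to prevent entry errors, and detailed query rules normally sit in documents not shown. A reader might infer that answers will be altered. The text shows only that the route is open.

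On mechanism, controls who wait for physiotherapy experience a real difference in care under treatment as usual. That is part of the comparison and should not be counted as reporting bias.

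**Conclusion.** The point holds in a limited form. The sentence in Internal validity attributes to the design a property it does not have. It conflicts with the article's own treatment of non-blinded assessors and with its Discussion. The primary endpoint and every patient-reported confirmatory endpoint are assessed open-label: five of the seven at least, and all seven if the CGI is also patient-reported.

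An open-label comparison is defensible here, since patients cannot be kept blind to an app or to physiotherapy. What is not defensible is declaring it free of detection bias.

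The size is unknown. The range of 9.1%–42.4% (SD 12) or 14.3%–75.5% (SD 8) shows how sensitive the test is to a bias of 1 to 3 points. It rests on that assumed bias, on no true effect and on complete data. It should not be read as an estimate of this trial's error rate.

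Confidence is high for the sentence itself. The CGI rater is an unresolved conflict, and monitor queries are a risk rather than an error in the text.

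**What to change.** 1. Replace the sentence in Internal validity. State that the patient-reported confirmatory endpoints are assessed by unblinded patients and are subject to detection bias, that any superiority claim carries that limit, and that the single-blinded label covers only endpoints actually rated by blinded staff. Bring the Discussion into line.
2. Reconcile Study setting and design with Study interventions and Follow-up measures. State who rated CGI-I at week 12 and who rated CGI-S at T0 and at T3. If the CGI-S raters differed, its change score is not a valid confirmatory endpoint, and the report must say so.
3. Report how many confirmatory questionnaire answers were changed after a monitor query, by arm, and repeat the primary analysis on the answers as first submitted. This assumes that the eCRF kept the first entries; if it did not, say so.

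Trial status says the article was re-submitted after the study closed, so locking entries at submission or introducing a blinded T3 rater is no longer possible. The remaining changes need clarified text and one extra sensitivity analysis. Their price is a more modest statement on internal validity.
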